# Efficacy of surgical excision and sub-dermal injection of triamcinolone acetonide for treatment of keloid scars after caesarean section: a single blind randomised controlled trial protocol

**DOI:** 10.1186/s13063-019-3465-6

**Published:** 2019-06-18

**Keywords:** Keloid, Scar, Caesarean section, Triamcinolone acetonide, Injection

## Abstract

**Background:**

One of the first-line options to treat keloid scars is corticosteroid injection after excision of the existing scar. A thorough literature search has shown a lack of research on the injection of corticosteroid injection immediately after the excision of the existing caesarean section keloid scars. Therefore, in the proposed study, we aim to investigate the effect of surgical excision and corticosteroid (triamcinolone acetonide) injection immediately after surgical removal of old caesarean section keloid scars on the recurrence of the scars. This is a protocol for a randomised controlled trial.

**Methods/design:**

Pregnant women (*n* = 150), who attend antenatal clinics at Westmead Hospital in New South Wales, Australia, have a keloid scar from a previous caesarean section, meet the inclusion criteria and sign the consent form, will be randomised to either the control or the intervention group. The control group will receive surgical excision of the keloid scar at the beginning of the procedure during skin incision. The baby will be delivered according to normal procedures, and routine wound closure will be performed in accordance with National Institute for Health and Care Excellence guidelines. The intervention group will receive surgical excision of the keloid scar after the delivery of the baby, and closure of the uterus layers, rectus sheath and the fat layer will be completed as explained above. Then, triamcinolone acetone will be injected sub-dermally at the time of wound closure. Two ampules of triamcinolone acetonide will be administered at a single dose; each ampule contains 10 mg/1 ml active medication. The surgeon will inject one ampule along the entire length of the upper edge of the skin incision and one ampule along the entire length of the lower edge of the skin incision, using a 25 G needle. After the procedure is completed, the surgeon will fill in the post-operation survey.

The participants will be followed up post-operation, daily on the ward and then at 6 weeks, 6 months and 12 months post-partum. Main outcomes are (1) keloid formation after caesarean section and (2) changes in the appearance and specification of the keloid scar after the intervention.

**Discussion:**

We anticipate that surgical excision and steroid injection will be a safe, lasting and cost-effective treatment in the management of caesarean keloid scars which will be useful for patients unable to undergo cosmetic surgery due to clinical or financial reasons.

**Trial registration:**

Australian New Zealand Clinical Trials Registry, ACTRN12618000984291. Registered on 12 June 2018.

**Electronic supplementary material:**

The online version of this article (10.1186/s13063-019-3465-6) contains supplementary material, which is available to authorized users.

## Background

Keloid scars affect 10–15% of all wounds and represent an exaggerated healing response that poses a challenge for physicians. They can appear anywhere on the body and can last for years after the initial injury [1]. Patients at risk of keloid scars are usually younger than 30 years and have darker skin. Darkly pigmented skin is the primary risk factor for keloids, which has a 15–20 fold increased risk due to melanocyte-stimulating hormone anomalies. Black, Hispanic and Asian persons are more likely to develop keloid scars than Caucasians. Keloid scars are more than just disfiguring cosmetically; many are also pruritic and painful. They also often result in severe emotional distress [2].

Keloid scars are associated with deteriorated mental health during the post-natal period and can contribute to negative body image, impaired intimate relationships and symptoms of depression. Patients with keloid scars have been reported to be unhappy with their scars due to their perceived stigma and psychological association [3–6]. Consequently, this can result in these patients being unsociable and may interfere with their communication skills, personal relationships and work, life and leisure activities. Patients are usually concerned about the diagnosis and persistent nature of the scars and report that non-empathic management by general physicians and frustrations of current treatment compound their distress [6].

Any kind of trauma that can reach the reticular dermis and cause cutaneous injury (such as insect bites, burns, surgery, vaccinations, skin piercings, acne, folliculitis, etc.) can create abnormal wound healing and trigger keloid scar formation in predisposed people. The abnormal wound healing is described by continuous and histologically localised inflammation and increased inflammatory cells, which result in the increase of fibroblasts, proinflammatory factors, newly made blood vessels and collagen deposits. These changes can stimulate chronic inflammation, which in turn causes the invasive growth of keloid scars. In addition, the upregulation of proinflammatory factors in pathological scars suggests that keloid scars are inflammatory conditions of the reticular dermis of the skin [7, 8].

Based on the cellular mechanism of keloid formation, one of the first-line options to treat keloid scars is corticosteroid injection into the affected area. The steroids have both direct anti-inflammatory and vasoconstrictive effects. Administration of corticosteroids results in the whitening of keloid scars, suggesting a decrease of blood flow in the scar due to vasoconstriction [7].

Another suggested treatment of keloid scars is surgical removal of the scar. However, since surgical removal of the keloid usually only provides temporary cosmetic relief and invariability followed by even more aggressive regrowth of scar tissue in 50–100% of cases, many clinicians perform surgical excision of the keloid scar followed by sub-dermal corticosteroid injections. This has been suggested to be effective for patients with small or single site lesions [9].

Some studies have used immediate wound edge corticosteroid injection after the excision in patients with hypertrophic scars and keloid scars, followed by regular injection of corticosteroid: usually a weekly injection for 2–5 weeks followed by monthly injections for 3–6 months [10]. This combination of surgical removal and corticosteroid injections has been shown to improve outcome. This dose of steroid is substantially more than the stat dose we plan to use in our study and requires multiple visits and repeated injections.

A thorough literature search has shown a lack of research on the surgical excision and injection of corticosteroid injection immediately after the excision of the existing caesarean section keloid scars. Therefore, in the proposed study, we aim to investigate the effect of corticosteroid (triamcinolone acetonide) injection immediately after surgical removal of old caesarean section keloid scars on the recurrence of the scars.

### Hypothesis

Given that triamcinolone acetonide has been used for treatment of keloid scar in other areas of the body [11, 12], we hypothesise that excision of a previous caesarean section keloid scar in conjunction with sub-dermal injection of triamcinolone acetonide will reduce the recurrence and formation of the keloid scar. We would also expect positive patient satisfaction from the treatment and a decline in symptoms of post-partum depression.

### Composite primary objective

A primary objective is to determine if surgical excision and sub-dermal injection of triamcinolone acetonide at the time of subsequent caesarean section is effective in preventing or reducing the amount of keloid formation in patients with a previous history of keloid scar after caesarean section. We also aim to investigate whether the appearance and specification of the keloid scar changes after the intervention (type of response).

### Secondary objectives

Secondary objectives of the trial are to:Evaluate the effect of surgical excision and keloid scar treatment on symptoms of depression in women with keloid scarsDetermine whether surgical excision and sub-dermal injection of triamcinolone acetonide at the time of caesarean section changes the appearance (width, length, height) and specification (redness, hardness and elevation of the scar compared to the surrounding skin as well as discomfort including itching, pain and swelling) of the keloid scarAssess side effects of the surgical excision and sub-dermal injection of triamcinolone acetonide at the time of caesarean sectionInvestigate patients’ satisfaction with the treatment and their perception with the changes in their keloid scar after surgical excision and sub-dermal injection of triamcinolone acetonide at the time of caesarean section.

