### Participants

The inclusion criteria for the study are (1) age between18–45 years old; (2) being pregnant at the time of recruitment; (3) presence of a keloid scar from a previous caesarean section; (4) planned caesarean section for the current pregnancy. Women of all ethnicities with a keloid scar following a previous caesarean section will be eligible to participate in the study.

The exclusion criteria for the study are (1) being primigravida and (2) having a previous caesarean section with no keloid scar. Since the aim of the study is to investigate the impact of treatment on the caesarean section keloid scar, the type of skin excision in the caesarean section (vertical or horizontal) will not be an inclusion/exclusion criterion.

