### Secondary outcomes

The secondary outcomes are:Percentage of women with depression, anxiety and stressPatients’ satisfaction with the treatment and changes in their keloid scars.

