#### Depression, Anxiety and Stress Scale-21 (DASS-21)

The DASS-21 is the short version of the DASS-42 questionnaire. It contains a set of three self-report scales and will be used to measure anxiety, depression and stress during pregnancy and after childbirth. The DASS-21 has been shown to have high internal consistency and to yield meaningful discriminations in a variety of settings. It should meet the needs of both researchers and clinicians who wish to measure current state or change in state over time on the three dimensions of depression, anxiety and stress. The tool has been used in previous studies on perinatal women in Australia, Canada, Chile, England, Germany, Iceland, New Zealand and the USA with reasonable response rates [14, 15]. Each of the three DASS-21 scales contains 7 items. The Depression scale assesses dysphoria, hopelessness, devaluation of life, self-deprecation, lack of interest/involvement, anhedonia and inertia. The Anxiety scale assesses autonomic arousal, skeletal muscle effects, situational anxiety and subjective experience of anxious affect. The Stress scale is sensitive to levels of chronic non-specific arousal. It assesses difficulty relaxing, nervous arousal and being easily upset/agitated, irritable/over-reactive and impatient. Respondents are asked to use 4-point severity/frequency scales to rate the extent to which they have experienced each state over the past week. Scores for Depression, Anxiety and Stress are calculated by summing the scores for the relevant items and then multiplying each scale score by 2. Then, each score can be transferred to the DASS profile sheet, enabling comparisons to be made between the three scales and also giving percentile rankings and severity labels as shown in the following table.

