### Procedures

All eligible women will be approached at the time of booking into the clinic for caesarean section at around 36 weeks and will be given information about the study. Those women who meet the inclusion criteria and sign the informed consent form will be randomised to either the intervention or the control group by the independent researcher as explained previously (Fig. 1). On the day of the caesarean section, the sealed envelope containing instructions for the type of treatment will be picked up by the surgeon. The surgeon opens the envelope when the woman is ready for the caesarean section.

The control group will receive surgical excision of the keloid scar at the beginning of the procedure during skin incision. The baby will be delivered as normal, and routine wound closure will be performed in accordance with National Institute for Health and Care Excellence (NICE) guidelines as follows: The uterus is closed in two layers followed by closure of the rectus sheath, all using continuous sutures with 1-Vicryl (Johnson & Johnson). The fat layer is closed with interrupted plain gut sutures 2 cm apart. The skin layer is then closed with 3-0 Monocryl (Ethicon) in a sub-cuticular fashion.

The intervention group will receive surgical excision of the keloid scar after the delivery of the baby. Closure of the uterus layers, rectus sheath and the fat layer are completed as explained above. Then, triamcinolone acetone will be injected sub-dermally at the time of wound closure. Two ampules of triamcinolone acetonide (Kenacort®-A 10 suspension, Aspen Pharma Pty Ltd) will be administered at a single dose; each ampule contains 10 mg/1 ml active medication. The surgeon will inject one ampule along the entire length of the upper edge of the skin incision and one ampule along the entire length of the lower edge of the skin incision, using a 25 G needle.

After the procedure is completed, the surgeon will fill in the post-operation survey. The excision of the scar and administration of the injection will be performed by the surgeon who is scheduled to perform the surgery on that day. All the surgeons in the Department of Women’s and Newborn Health will be trained on how to perform the excision and injection of the triamcinolone. The Principal Investigator of the study will assess the fidelity to the intervention by supervising procedures.

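### The depression objective names an effect of excision that has no comparator, and its listed outcome, a percentage, wastes the DASS-21 scores the trial already collects

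*Protocol article*

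**What the plan says.** Four parts of the protocol article bear on this point.

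- **Objective and hypothesis.** The first item under Secondary objectives is to evaluate "the effect of surgical excision and keloid scar treatment on symptoms of depression in women with keloid" scars. The Hypothesis section adds that the investigators expect "a decline in symptoms of post-partum depression".
- **Treatment.** Under Procedures, "The control group will receive surgical excision of the keloid scar at the beginning of the procedure during skin incision". In the other arm, "The intervention group will receive surgical excision of the keloid scar after the delivery of the baby", and triamcinolone is then injected at wound closure.
- **Measurement.** The DASS-21 "will be used to measure anxiety, depression and stress during pregnancy and after childbirth". The Follow-up section places the later assessments at 6 weeks, 6 months and 12 months post-partum. The DASS-21 section also gives numeric scoring: "Scores for Depression, Anxiety and Stress are calculated by summing the scores for the relevant items and then multiplying each scale score by 2".
- **Outcome and analysis.** Secondary outcomes lists the percentage "of women with depression, anxiety and" stress. Data analysis compares binary outcomes between groups by relative risk and a chi-squared or Fisher test. It also names depression, anxiety and stress among the outcomes of interest, and provides a t test for continuous data and a Mann–Whitney test for skewed ordinal data.

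**The concern.** The stated objective and the randomised contrast are different things. A question about excision plus scar treatment needs a group without excision, and there is none. With the objective worded this way, the only analysis that seems to address it is change since pregnancy within the treated women. The word for a fall in symptoms in the Hypothesis points the same way. That change has no control for childbirth or the passage of time.

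The second mismatch lies in the outcome. The objective and hypothesis are about symptoms, but the listed outcome counts women on one side of a line. Movement within a severity band is lost, and a chi-squared test leaves the antenatal score unused. Two wrong conclusions are possible. An ordinary post-partum change could be reported as a benefit of treating the scar, or an imprecise comparison of percentages could be reported as no effect on mood.

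**Working it through.** **1. Which effect is identified.** Write E for excision and T for triamcinolone. The control arm receives E and the intervention arm receives E + T. The difference between arms is (E + T) − E = T given E. Neither E nor the package E + T against no treatment can be estimated. (The arms are also described as excised at different points of the operation; any effect of that timing travels with T.)

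**2. What a decline can mean.** The pre-treatment score comes from pregnancy and every later score from after birth. Within one arm, change = treatment + (childbirth and time), and the two parts cannot be separated. Between arms at the same visit, the second part is common to both and cancels in expectation.

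**3. The plan's own figure.** Sample size: 45% v 70%, 80% power, two-sided 5%, 10% non-compliance, 75 per arm. With mean proportion 0.575:

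n = [1.96√(2 × 0.575 × 0.425) + 0.8416√(0.45 × 0.55 + 0.70 × 0.30)]² / 0.25² = 61 per arm, or 68 with continuity correction.

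Then 68 × 1.1 = 75 and 68 / 0.9 = 76, so 75 is reproduced. It is set for keloid efficacy. No figure is given for depression.

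**4. Power for the percentage.** The rates are assumed. With n = 75 per arm, power = Φ{[d√n − 1.96√(2p̄(1 − p̄))] / √(p₁q₁ + p₂q₂)}.

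- 20% v 10%: (0.866 − 1.96 × 0.505) / 0.500 = −0.247, so power is 40%.
- 30% v 20%: (0.866 − 1.96 × 0.612) / 0.608 = −0.549, so power is 29%.

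**5. The same shift analysed as a score.** Assume a normal score with the cut-off at the same place in both arms.

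- 20% v 10%: shift = 1.282 − 0.842 = 0.440 SD. Power = Φ(0.440√37.5 − 1.96) = Φ(2.694 − 1.96) = 77%.
- 30% v 20%: shift = 0.842 − 0.524 = 0.317 SD. Power = Φ(1.943 − 1.96) = 49%.

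**6. Adjusted for the antenatal score.** Assume correlation r = 0.5. The residual SD is √(1 − 0.25) = 0.866.

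- 20% v 10%: Φ(2.694 / 0.866 − 1.96) = Φ(1.151) = 87.5%.
- 30% v 20%: Φ(1.943 / 0.866 − 1.96) = Φ(0.283) = 61%.

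**7. Sensitivity.** If the 10% allowance is read as loss, leaving 67 per arm:

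| Assumed rates | n per arm | Percentage | Score | Adjusted score |
|---|---|---|---|---|
| 20% v 10% | 75 | 40% | 77% | 87.5% |
| 20% v 10% | 67 | 37% | 72% | 84% |
| 30% v 20% | 75 | 29% | 49% | 61% |
| 30% v 20% | 67 | 27% | 45% | 56% |

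For a halving of the control rate with 75 per arm, the percentage has 21% power at a 10% rate, 40% at 20% and 60% at 30%. An unadjusted score has 80% power for a difference of (1.96 + 0.8416)√(2/75) = 0.46 SD.

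**The case against.** A reader might infer that the depression question cannot be answered at all, or that a benefit would go unseen. The documents do not support that, for these reasons.

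- This is a randomised parallel-group trial analysed by intention to treat. Comparing post-partum DASS-21 between arms at the same visit validly estimates the added effect of triamcinolone.
- The antenatal timing of the baseline does not bias that comparison, because both arms go through the same transition.
- No within-group test of depression is planned. The only within-group comparison under Data analysis concerns keloid formation.
- Eligibility sets no symptom threshold: "2) being pregnant at the time of recruitment; (3) presence of a keloid scar from a previous caesarean section" are required, along with age and a planned caesarean. Women who start with few symptoms dilute an effect and so cost power, but they do not invalidate the comparison. How many such women there will be is not stated.
- Data analysis names depression without tying it to a percentage and offers tests for scores, so a score analysis is not ruled out.
- Baseline adjustment, the DASS-21 cut-off and the main visit are details that an analysis plan commonly supplies. Their absence from an article is not a fault.
- Low power for a secondary outcome is usual, and the rates used above are assumed.

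All of this stands, and it limits the point. Two statements in the article remain unaffected: an objective worded as an effect of excision when everyone is excised, and an outcome fixed as a percentage when the objective is about symptoms. The loose use of the package wording in other objectives explains the first but does not repair it.

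**Conclusion.** The point holds in limited form. The wording of the depression objective does not match the design: only the effect of triamcinolone added to excision is identified, and the expected decline must not be read as change since pregnancy. The listed percentage is a weaker measure than the scores already collected. Under assumed rates of 20% v 10% with 75 per arm, power rises from about 40% to 77% as a score and to 87.5% with baseline adjustment. Under 30% v 20% it rises from 29% to 49% and 61%.

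These sizes rest on assumed rates, a normal score, a shift that moves the whole distribution and r = 0.5. DASS-21 scores are likely to be skewed, which would reduce the gain. The between-arm comparison of percentages is valid but imprecise. This is a secondary objective, and the change is a cheap improvement that should be made; it does not threaten the trial's main question.

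**What to change.** 1. Reword the secondary objective, and the matching phrase in the Hypothesis, to the added effect of triamcinolone over excision alone on post-partum DASS-21 scores.
2. In Secondary outcomes and Data analysis, make the measure the difference between arms in each DASS-21 score at one named post-partum visit, for example 12 months, with 6 weeks and 6 months as supporting visits.
3. Adjust for the antenatal score by analysis of covariance, with a rank-based analysis as a check for skew.
4. Keep the percentage above a stated DASS-21 band as description.
5. State that no conclusion about treatment will be drawn from within-arm change since pregnancy.

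The cost is the wording of one objective, one sentence of the hypothesis and one analysis. No new data, visits or participants are needed. The trial gives up a claim about excision itself, which its design cannot support.

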## Methods/design

### Setting

The patients will be recruited from the antenatal clinics that are booked for delivery at Westmead Hospital, a large tertiary unit serving a multiethnic, low-middle income population in addition to referred high-risk pregnancies in Western Sydney, New South Wales, Australia. Figure 1 is a flow diagram of the trial. The Standard Protocol Items: Recommendations for Interventional Trials (SPIRIT) checklist is provided as Additional file 1.

**Fig. 1 Fig1:**
[figure not shown]
Flow diagram of the trial

### Study design

This will be a superiority randomised controlled clinical trial with parallel intervention assignment.

### Ethical approval

The study protocol, amendments and consent form were approved by the Western Sydney Local Health District Human Research Ethics Committee.

### Participants

The inclusion criteria for the study are (1) age between18–45 years old; (2) being pregnant at the time of recruitment; (3) presence of a keloid scar from a previous caesarean section; (4) planned caesarean section for the current pregnancy. Women of all ethnicities with a keloid scar following a previous caesarean section will be eligible to participate in the study.

The exclusion criteria for the study are (1) being primigravida and (2) having a previous caesarean section with no keloid scar. Since the aim of the study is to investigate the impact of treatment on the caesarean section keloid scar, the type of skin excision in the caesarean section (vertical or horizontal) will not be an inclusion/exclusion criterion.

